## Abstract

**Background:**

The childbirth experience has significant effects on the life of the mother and family. However, there are no Iranian studies which evaluate and measure women’s childbirth experiences to provide accurate data on this important matter. The aim of this study is to develop a new guideline to improve women’s childbirth experiences by meeting their needs and expectations.

**Methods/design:**

The present study will use the mixed method with the explanatory sequential approach. Phase one is a cross-sectional survey with random cluster sampling of the health centers in Tabriz. Eight hundred primiparous women will be selected to measure their childbirth experiences and predictors factors. Phase two is a qualitative study to explore women’s perceptions of the aspects and determinants of the childbirth experience. Phase two participants will be selected using purposive sampling from the women who participated in phase one. Phase three involves developing a new guideline to improve women’s childbirth experiences. The new guideline will be developed based on the following elements: a) the results of the qualitative and quantitative data from phase one and two, b) a review of the related literature, and c) expert opinions that have been collected using the Delphi technique.

**Discussion:**

By exploring women’s childbirth experiences and the influencing factors, a culturally sensitive evidence-based guideline can be developed. The provision of the evidence-based guideline resulting from this study might be effective in improving the quality care of the services for pregnant women.

**Ethical code:**

IR.TBZMED.REC.1396.786.

## Plain English summary

The first childbirth experience can affect not only a broad range of personal and social aspects of a woman’s life in the future but also her perception of the future childbirth experience. Furthermore, women with a negative birth experience are more likely to request a cesarean. Asking for a C-section without indication can lead to an increased rate of negative childbirth experience.

Although childbirth is a global event and some approaches to improve the childbirth experience have been adopted in the majority of developed countries, the childbirth experience is a momentous mental and personal concept. The childbirth experience differs from one woman to another and is affected by internal, cultural, and social learning factors. There are currently no Iranian studies which accurately evaluate and measure women’s childbirth experiences using standard validated tools. The current study is designed to develop a new guideline to improve women’s childbirth experiences.

The present study will use a mixed method with an explanatory sequential approach. This study will have three phases. Phase one is divided to two sections: the aim of first section is to adapt the scales to the Iranian context and determine their psychometric characteristics. The second section is a descriptive-analytic cross-sectional study to identify the women’s childbirth experiences and influencing factors. Phase two is an exploratory qualitative study to explore women’s childbirth experiences in more detail. Phase three is about developing an evidence based and culturally sensitive guideline based on literature review, the results of phase one and two and experts’ opinion using the Delphi method.

## Background

Childbirth experience is defined as an “individual life event, incorporating interrelated subjective psychological and physiological processes, influenced by social, environmental, organizational and policy contexts” [1]. Traditionally, maternity health care services focused their efforts and resources on reducing perinatal mortality and paid less attention to mothers’ childbirth experiences and beliefs about motherhood [2, 3]. However, women’s experiences of the childbirth process are long-term memories [4] and can influence their mental health status [5]. Negative childbirth experiences are associated with post-traumatic stress disorder (PTSD) [6], poor mother-infant attachment [7], sexual dysfunction, mood and behavior disorder [8], postnatal depression [9], and decisions about future pregnancies [10]. Furthermore, women with a negative birth experience are more likely to request a cesarean [11]. This is a more common issue in Iran. The prevalence of cesarean section in Iran is estimated at 48% [12] and a previous negative childbirth experience as a non-medical factor is one of the most important reasons Iranian women request cesarean sections [12]. Asking for a C-section without indication can lead to an increased rate of negative childbirth experience. Moreover, women undergoing a C-section displayed a more negative attitude towards themselves and their infants. They also demonstrated poorer parental behaviours and were more prone to postpartum mood disorders [13–15].

The first childbirth experience can affect not only a broad range of personal and social aspects of a woman’s life in the future [8] but also her perception of the future childbirth experience. In that, some studies have shown that the childbirth experience of multiparous women depends on their first childbirth experience [16].

Women’s childbirth experiences and influencing factors are well known in developed countries [14, 16–21]. According to the findings of these studies, factors such as instrumental childbirth [17], fear of childbirth [18], complications during pregnancy [19], previous negative birth experience [16, 17], perceived poor support and control [20, 21], neonatal complications [14] are well known risk factors of a negative birth experience.

Developed countries have developed and applied standard scales for an accurate measurement of women’s childbirth experience. More than 30 standard scales for assessing the experience of childbirth have been introduced, and almost all are based on the experiences of women in developed countries. Some standard scales commonly used in research include “The Labor Agent Scale (LAS)”, “The Wijma Delivery Expectancy / Experience Questionnaire (W-DEQ”, “The Childbirth Perception Scale”, “The Childbirth Trauma Index (CTI)”, and “Childbirth Experiences Questionnaire (CEQ)” [22].

However, there are only a limited number of developing countries that have investigated the childbirth experience. Results of a descriptive study in Turkey on primiparous women showed that they received many midwifery interventions during labour in both public and private hospitals. In addition, they rarely received food during labour and had no skin-to-skin contact with their infants. They also experienced a high level of fear and anxiety. Moreover, the medical staff helped these women only for body movements and position change [23]. A qualitative study with a phenomenological approach was conducted on childbirth experience and its meaning among women in Uganda. The mothers in this study considered childbirth pain as a natural phenomenon from a social perspective. Providing mothers with physical, mental, and social support, peace, sympathy, and encouragement resulted in a positive childbirth experience; whereas, inappropriate care, poor communication, and the lack of privacy led to a negative maternal childbirth experience [24]. A qualitative study with a content analysis approach explained the childbirth experience of women in the west of Kenya. The experience of this group of women was affected by external factors, such as the behaviour of clinical staff, their support, and childbirth facilities and environment [25].

However, there are currently no Iranian studies which accurately evaluate and measure women’s childbirth experiences using standard validated tools. Although childbirth is a global event and some approaches to improve the childbirth experience have been adopted in the majority of developed countries, the childbirth experience is a momentous mental and personal concept [1]. The childbirth experience differs from one woman to another and is affected by internal, cultural, and social learning factors. In that, women’s expectations and preferences during labour and delivery depend on the values of their community. Moreover, the childbirth experience is a complex concept, which includes a broad range of dimensions. The frequency of developed instruments to measure childbirth experience reflects the attempts made to identify and evaluate its complex dimensions [26–28].

Considering that the cultural, economic, and social differences of different societies require examining human experiences in each individual society, there is a need for a rigorous multiphasic study with a mixed method approach to evaluate Iranian women’s childbirth experiences systematically, and to develop an evidence- based guideline to improve their experiences.

### Objectives

The aim of the study is to develop a new guideline to improve women’s childbirth experiences. The following items are the specific objectives of the study.

### The specific objectives are

#### Phase 1

To adapt the “CEQ 2.0” and “SCIB” scales to the Iranian context and determine their psychometric properties.To measure the childbirth experience score among primiparous women who gave birth in public and private hospitals of Tabriz, Iran.To determine perceived support and control in birth among primiparous women.To determine the relationship between perceived support and control in birth with childbirth experience among primiparous women.To determine the relationship between sociodemographic characteristics and childbirth experience among primiparous women.To determine the relationship between antenatal, intrapartum factors and childbirth experience among primiparous women.

#### Phase 2

7.To explore women’s perceptions regarding the aspects and determinants of childbirth experience among primiparous women.

#### Phase 3

8.To develop an evidence-based guideline to improve women’s childbirth experience by meeting their needs and expectations.

## Methods/ design

### Study design

The present study will use a mixed method with an explanatory sequential approach. The paradigm of the mixed method is based on the principle of pragmatism. Based on this paradigm, the mixed use of quantitative and qualitative approaches leads to a better understanding of the problem [29, 30].

The sequential explanatory design is a mixed method that firstly collects and analyses quantitative data and then qualitative data to explain and/or generalise quantitative data. In this model, the researcher first identified quantitative data that required further explanation and then collected qualitative data from participants, who could contribute to a deeper explanation of the collected data [30].

This study will have three phases. Phase one is divided to two sections: the aim of first section is to adapt the scales to the Iranian context and determine their psychometric characteristics. The second section is a descriptive-analytic cross-sectional study to identify the women’s childbirth experiences and influencing factors (socio-demographic, antenatal, and intrapartum factors). Phase two is an exploratory qualitative study to explore women’s childbirth experiences in more detail. Phase three is about developing an evidence based and culturally sensitive guideline based on literature review, the results of phase one and two and experts’ opinion using the Delphi method (Fig. 1).

**Fig. 1 Fig1:**
[figure not shown]
Study visual diagram

### Phase one: quantitative study

A descriptive-analytic cross-sectional study will assess childbirth experiences and its relationship with support and control in birth, sociodemographic, antenatal and intrapartum factors among the participants. The target population will be primiparous women who give birth in public and private hospitals in Tabriz, Iran. Childbirth Experience Questionnaire 2.0 (CEQ 2.0) and Support and Control in Birth (SCIB) scales will be used to collect the data. The data collection tools will be validated and standardized for use among the Iranian population.

#### Sample size and sampling method

According to Nunnally & Bernstien, for a factor analysis in the validation of scales, 10 samples per item are required [31]. Given the 33 items in SCIB, 330 samples are needed. However, a sample of 660 people is required due to the sampling plan and the design effect of 2. Considering that the sampling plan in the first phase is cluster, the design effect must be considered. “The loss of effectiveness by the use of cluster sampling, instead of simple random sampling, is the design effect” [28]. Using a cluster sample usually needs a larger sample size than a simple random sampling and for a well-designed study, the design effect usually ranges from 1 to 3 [32, 33]. Considering a minimum 20% attrition rate, the total required sample size is calculated to be a minimum of 800 participants.

First, the rate of vaginal childbirth in public and private hospitals will be extracted separately. Then, all of the urban and suburban Tabriz health centers will be listed and numbered (114 centers). Using cluster sampling and the website www.random.org, approximately half of the centers will be randomly selected. A list of potential participants will be arranged based on the health records at each selected center. From the list, the required sample size for each center will be determined using the proportional sampling method by the rate of vaginal childbirth in public and private hospitals and the samples will be randomly selected. Using the phone number registered in each record, the researcher will call the potential participants and invite them to participate in the study.

The eligible participants will be provided with full explanations about the study objectives and procedures. Socio-demographic questionnaire, Childbirth Experience Questionnaire 2.0 (CEQ 2.0), and Support and Control in Birth questionnaire (SCIB) will be filled out in a relatively quiet environment by a research staff member and collected in person. A number of participants are likely to be illiterate, so the questionnaires will be completed by the researcher in order for the data collection method to be the same for all individuals. Obstetrics information will be collected by referring to individuals’ medical records. Also, informed consent will be obtained before collecting information from women’s medical records.

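### The phase one total of 800 leaves 640 women after 20% attrition, short of the 660 the plan requires; its own inputs give 825

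*Protocol article*

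**What the plan says.** The sample size is built up in the protocol article under Phase one, Sample size and sampling method, in four steps.

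- The criterion is a rule for factor analysis: "for a factor analysis in the validation of scales, 10 samples per item are required".
- It is applied to the longer of the two scales: "Given the 33 items in SCIB, 330 samples are needed".
- Cluster sampling of health centers then doubles the number: "However, a sample of 660 people is required due to the sampling plan and the design effect of 2".
- Losses are allowed for last: "Considering a minimum 20% attrition rate, the total required sample size is calculated to be a minimum of 800 participants".

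The section on scales and data collection confirms that SCIB has 33 items. The abstract repeats the total as the planned number: "Eight hundred primiparous women will be selected to measure their childbirth experiences and predictors factors". The article does not give the formula that takes 660 to 800.

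**The concern.** An attrition rate is a share of the women entered, not of the women who must remain. The required number therefore has to be divided by the retained fraction. The printed total is too low for that and looks like the result of adding 20% of the target instead.

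This rule, with its design effect, is the only sample-size justification given for phase one. If the total falls short under the plan's own attrition figure, the one stated criterion is not met, and a reader cannot recover the printed number from the printed inputs. The Discussion also lists the sample size among the study's strengths.

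**Working it through.** **Inputs**, all from Sample size and sampling method: 10 women per item; 33 SCIB items; design effect 2; attrition 20%, given as a minimum; total 800, also given as a minimum.

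**Reproducing the plan's figures**

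1. Base number: 33 × 10 = 330. Agrees.
2. After the design effect: 330 × 2 = 660. Agrees.
3. Total, multiplying by (1 + attrition): 660 × 1.20 = 792, which rounds up to 800. This is the likely route to the printed figure, but it is inferred.
4. Total, dividing by (1 − attrition): 660 / 0.80 = 825. This does not give 800.

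Multiplying up does not restore the target: 792 × 0.80 = 633.6. Rounding up to 800 closes only part of that gap.

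**What 800 delivers**

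| Quantity | Calculation | Result |
|---|---|---|
| Women remaining at 20% attrition | 800 × 0.80 | 640 |
| Shortfall | 660 − 640 | 20 (20/660 = 3.0%) |
| Effective number at design effect 2 | 640 / 2 | 320 |
| Effective women per SCIB item | 320 / 33 | 9.7 |
| Largest attrition at which 660 remain | 1 − 660/800 | 17.5% |
| Total needed at 20% attrition | 660 / 0.80 | 825 |
| Shortfall in the total | 825 − 800 | 25 |

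Because 20% is described as a minimum, 640 is the most the plan can expect to keep. As an illustration only, with an assumed rate of 25%, 800 would leave 600 women, or 300 effective and 300/33 = 9.1 per item.

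**Chance of reaching 660.** Assume each woman is retained independently with probability 0.80. The probability that at least 660 remain is then about 0.04 from 800 and about 0.52 from 825. So 825 meets the requirement in expectation and carries no further margin.

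**The case against.** The strongest reply is that the discrepancy has little practical weight.

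- **The target is a rule of thumb.** No power, error rate or interval width depends on 660, and no factor-analysis conclusion is known to turn on 9.7 against 10 women per item. This stands and keeps the point minor.
- **The design effect is itself uncertain.** The article says such values usually lie between 1 and 3. With 640 women, the 330 effective women are reached if the design effect is 640/330 = 1.94 or less, and before any design effect there are 640/33 = 19.4 women per item. This also stands: the gap between 1.94 and 2 is much smaller than the article's own range.
- **The other scale is well covered.** CEQ 2.0 has 23 items, so the same rule needs 23 × 10 × 2 = 460 women, and 640 gives 320/23 = 13.9 effective women per item. This is correct. The shortfall concerns SCIB only.
- **The total is called a minimum.** This does not help. A minimum must suffice under the stated assumptions, and they imply 825. The abstract also plans for 800 as such.
- **Attrition is a loose term in a cross-sectional survey.** Losses would come mainly from non-response, exclusions or incomplete records, and the article does not say whether the 800 are women approached or women enrolled. The figure of 640 does rest on the plain reading that 20% of the 800 are lost. But the article presents 800 as the total after allowing for attrition, and whichever kind of loss is meant, taking 20% from 800 leaves 640.

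**Conclusion.** The concern holds. The printed total does not follow from its inputs: they require 825, and 800 leaves 640 women, 20 below the number the same paragraph calls required. The effective sample is 320, or 9.7 per SCIB item.

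This rests on the article's own design effect of 2 and on reading the 20% as a share of the 800. That the error came from multiplying by 1.20 is an inference, and the verdict does not depend on it.

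The importance is minor. The shortfall is about 3%, is confined to SCIB, lies within the article's own uncertainty about the design effect, and is unlikely by itself to change any phase one conclusion. What needs correcting is a sample-size statement that misses its own criterion.

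**What to change.** Correct the last step in Sample size and sampling method in one of two ways.

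1. Give the required total as 660/0.80 = 825, and change the abstract to match. This adds 25 women.
2. Keep 800, and state that at 20% attrition it yields 640 women (effective number 320, or 9.7 per SCIB item at a design effect of 2) and that it reaches 660 only if attrition is at most 17.5%. This costs one sentence and no extra recruitment.

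In either case, say whether the total counts women selected or women enrolled, so that it is clear what the 20% applies to.

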## Discussion

The childbirth process is described as a complex, multidimensional and individual experience with important outcomes of a safe birth and gaining favorable experiences during labor and birth. However, psychological outcomes that women experience are frequently ignored [1, 45] which may have a negative impact on women’s attitudes towards vaginal birth; and it may influence their personal life in the future. The present study will provide detailed information on the experiences of a large group of Iranian primiparous women and the factors that are associated with the experiences.

The proposed study has a few strengths. It will fill crucial knowledge gaps in supporting women during childbirth in an Iranian context. Therefore, it is expected to have important clinical implications. The development of an evidence-based multi-method guideline can be used as a starting point for the development of a guideline for maternity care. It is also designed with a mixed method approach; therefore, it supports the integration of different, even contradictory approaches and methods to understand the concepts [29, 30]. Quantitative and qualitative data collection will assist us in bettering our understanding of women’s experiences during childbirth.

This is among a few studies into the childbirth experience that not only explained women’s experience but also will collect expert opinions. In addition to the development of guidelines based on women’s experience and preferences, the method will engage the experts in the process of guideline development and will investigate the feasibility and cost-effectiveness of the recommendations within Iranian culture.

In addition to teaching hospitals, women admitted to private hospitals will be also included in the current study. In Iran, care conditions and protocols depend on the hospital. As a result, the inclusion of patients admitted to both public and private hospitals can produce more accurate and comprehensive results. Assuming that lifestyle and social environments may affect the expectations and preferences of women and their perception of the childbirth experience, women from health centres in both urban and suburban areas will be included.

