The proposed study has a few strengths. The use of standard scale in this study can lead to a more accurate measurement of childbirth experience. Large sample size, random cluster sampling, sample collection from both urban and suburban health centers and women who give birth in public and private hospitals in Tabriz can be considered strengths of the study. Also, the present study has a few limitations. The results will be restricted to the experience of Iranian mothers. This study will be performed on primiparous and low risk women. Therefore, the results will not be generalized to multiparous or high risk women.

The provision of the evidence-based guideline resulting from this study may be effective in improving the quality care of services for pregnant women where they are encouraged to have vaginal births. The results of the study will provide policymakers and health care stakeholders with a standard guideline to improve the experiences of Iranian primiparous women and its possible positive effect on natural birth.

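### Drawing the health centres from one combined urban and suburban list leaves the mix of centres to chance; stratifying the draw would give a small gain in precision at no cost.

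*Protocol article*

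**What the plan says.** The section Sample size and sampling method (phase one) sets out the draw in steps. The frame is a single one: "all of the urban and suburban Tabriz health centers will be listed and numbered (114 centers"). From it, using a randomisation website, "approximately half of the centers will be randomly selected", so about 57 of 114. No strata are named for this step.

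The only control of composition comes later, inside the selected centres, where each centre's sample size is "determined using the proportional sampling method by the rate of vaginal childbirth in public and private hospitals". That concerns the type of hospital and not the area of the centre.

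The Discussion gives the reason for using both kinds of area. It assumes that "lifestyle and social environments may affect the expectations and preferences of women and their perception of the childbirth experience", and therefore "women from health centres in both urban and suburban areas will be included". Its list of strengths repeats the point: "Large sample size, random cluster sampling, sample collection from both urban and suburban health centers".

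**The concern.** The protocol names area as possibly relevant to the outcome and relies on coverage of both areas when it claims broad results. The label is known for every centre before the draw, but the draw does not use it. The share of suburban centres in the sample will therefore differ from the share in the frame by chance. If the two areas differ in their mean scores, this chance variation passes into the estimated overall means of the CEQ and of the Support and Control in Birth (SCIB) scale. At stake is a little avoidable variance, and a representativeness claim that rests partly on luck where it could rest on the design.

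**Working it through.** **The plan's own sample size.** "Given the 33 items in SCIB, 330 samples are needed" (33 × 10 = 330), and "a sample of 660 people is required due to the sampling plan and the design effect of 2" (330 × 2 = 660). The stated minimum of 800 follows as 660 × 1.2 = 792, rounded up. With 20% attrition, 800 × 0.8 = 640 women remain; 640 is used below. The total of 800 does not depend on the present point.

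**Inputs from the article:** 114 centres, about half drawn (57), design effect 2, 640 women after attrition.

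**Assumptions, not in the article:** the number K of suburban centres, varied from 17 to 57; a CEQ standard deviation (SD) of 0.45; an urban/suburban difference of 0.1 or 0.2 CEQ points (about 0.2 or 0.4 SD); similar numbers of women per centre, so that the share of centres stands in for the share of women.

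**Step 1: chance variation in the mix.** The number of suburban centres drawn is hypergeometric (114, K, 57). For K = 23:

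- mean = 57 × 23/114 = 11.5
- SD = √[57 × (23/114) × (91/114) × (57/113)] = √4.63 = 2.15 centres
- SD of the share = 2.15/57 = 0.038
- central 95% range: 7 to 16 centres, or 7/57 = 12% to 16/57 = 28%

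| K (share of frame) | SD of share | 95% range of drawn share | P(off by >5 points) | P(off by >10 points) |
|---|---|---|---|---|
| 17 (15%) | 0.0335 | 8.8–21.1% | 0.11 | 0.001 |
| 23 (20%) | 0.0378 | 12.3–28.1% | 0.16 | 0.004 |
| 34 (30%) | 0.0430 | 21.1–38.6% | 0.31 | 0.024 |
| 46 (40%) | 0.0462 | 31.6–49.1% | 0.34 | 0.035 |
| 57 (50%) | 0.0470 | 40.4–59.6% | 0.26 | 0.024 |

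**Step 2: effect on the overall mean CEQ score.** The variance of the mean is 0.45² × 2/640 = 0.000633, so the standard error is 0.0252. The part due to the random mix is (difference × SD of share)². Stratifying removes that part, apart from rounding of one centre. The relative fall in the standard error is 1 − √(1 − part/0.000633).

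| K | Difference 0.1: share of variance, fall in SE | Difference 0.2: share of variance, fall in SE |
|---|---|---|
| 17 | 1.8%, 0.9% | 7.1%, 3.6% |
| 23 | 2.3%, 1.1% | 9.0%, 4.6% |
| 57 | 3.5%, 1.8% | 14.0%, 7.2% |

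The fall is thus about 1–2% for 0.1 points and about 4–7% for 0.2 points.

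**Step 3: are these differences compatible with a design effect of 2?** With equal clusters there are 640/57 = 11.2 women per centre. A design effect of 2 then implies an intraclass correlation of 1/(11.2 − 1) = 0.098 and a between-centre variance of 0.098 × 0.45² = 0.0198. A difference of 0.2 points with half the centres suburban needs 0.2² × 0.25 = 0.0100, about half of that variance, which is possible. A difference of 0.3 points at the same share needs 0.3² × 0.25 = 0.0225, or 114% of it, which is not. The calculation therefore stops at 0.2.

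**The case against.** The strongest reply is that nothing here is wrong. A simple random draw of centres is unbiased, and taking half the frame keeps the mix close to its true value: the chance of missing by more than 10 points is at most 0.035 for every K examined. The Discussion promises only that both areas are included. With 11 or more suburban centres in the frame, the chance of drawing none is below 0.0003. The study is sized for factor analysis, not for the precision of a mean, and most phase-one objectives are psychometric or concern associations. The full protocol behind the article may also describe strata. All of this stands, and it limits the point to a refinement. It does not remove the point: the article describes the frame, its size, the tool and the fraction drawn, and on that description the draw is unstratified.

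Three stronger readings are tempting, and the document does not support them.

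- *That urban and suburban women are expected to differ, perhaps markedly.* The Discussion says only that environment may have an effect, and gives no size or direction. A large gain would need a difference of about 0.3 points with half the centres suburban, which step 3 shows to be incompatible with the plan's design effect under the assumed SD and equal cluster sizes.
- *That too few suburban centres might be left for a comparison.* The specific objectives list no urban/suburban comparison. Proportional stratification would not raise the expected number of suburban centres either: half of 23 is 11 or 12, as it is now on average.
- *That 12% to 28% is the range for the sample of women.* It is the range for centres. The share of women depends on per-centre numbers that the article does not give.

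**Conclusion.** The point holds as a minor, free improvement. The draw as described is valid, but it ignores a known label that the protocol itself treats as possibly relevant to the outcome. The size rests on the assumed number of suburban centres, SD and area difference, and on similar numbers of women per centre; of the quantities that drive it, the article supplies only the frame, the fraction drawn, the design effect and the attrition rate. Within those limits the loss of precision is small. The more certain benefit is that the balance between areas would be fixed by design. No effect on the psychometric or association objectives has been shown.

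**What to change.** In Sample size and sampling method, number the urban and the suburban centres in two separate lists and draw the same fraction (half) at random from each. Keep the per-centre allocation rule the same in both areas, and treat area as a stratum in the analysis, so that the reported standard errors reflect the design. State the number of centres in each list.

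The cost is one additional random draw. The number of centres (about 57) and the total of 800 stay as they are. Centres keep equal selection probabilities to within rounding, so stratifying adds no need for weights.
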